### Patients and public involvement

Following the development of the basic intervention structure, we held a discussion group with 10 members of the general public aiming to improve the acceptability and effectiveness of the RE-MAP intervention. We invited five meat eaters and five meat reducers to attend the discussion group, aiming to include people representing the target population of the intervention as well as people that successfully reduced their meat consumption. Public contributors were recruited using an established mailing list. The discussion group informed the development of each intervention component and of other aspects of the trial including:What type of meat alternatives to offer as part of the intervention.How to design the educational intervention components to be engaging and easily accessible to different publics.What language to use as part of the success stories vignettes and how to increase their relatability.What cookbooks and recipes to use as part of the intervention.The likely burden of trial participation and how to best compensate trial participants.

Contributors to the aforementioned public involvement activities will not be involved in other aspects of the trial implementation (such as recruitment) and will be asked not to enrol as trial participants, as they will have already reviewed much of the intervention material.

### Outcomes

#### Primary outcome

Change in mean daily grams of meat consumed between the baseline (T0) and the 4-week follow-up (T1).

#### Secondary outcomes

Change in mean daily grams of meat consumed between the baseline (T0) and the 8-week follow-up (T2).Change in the intention to eat a low meat diet between the baseline (T0) and both follow-up (T1, T2).Change in attachment to meat, eating identities and in attitudes, perceived behavioural control, and subjective social norm of eating a low meat diet between the baseline (T0) and both follow-up (T1, T2).

#### Exploratory outcomes

Change in participants’ blood lipid profiles (total cholesterol, High-density lipoprotein (HDL) cholesterol, triglycerides, Low-density lipoprotein (LDL) cholesterol, non-HDL cholesterol, LDL:HDL cholesterol ratio) between the baseline (T0) and both follow-up (T1, T2).Change in systolic and diastolic blood pressure between the baseline (T0) and both follow-up (T1, T2).Change in participants’ body mass index between the baseline (T0) and both follow-up (T1, T2).Change in participants’ body fat percentage between the baseline (T0) and both follow-up (T1, T2).Change in the number of meals containing foods from other food groups between the baseline (T0) and both follow-up (T1, T2).Change in participants’ mean daily energy, macronutrients and micronutrients intake between the baseline (T0) and both follow-up (T1, T2).Change in participants’ intentions, attitudes, perceived behavioural control and subjective social norms of using meat alternatives between the baseline (T0) and both follow-up (T1, T2).Change in participants’ desire for meat substitutes to be similar to meat between the baseline (T0) and both follow-up (T1, T2).

### Measurements

Table 2 provides a summary of the trial activities and of the measurement that will be collected at each stage of the trial.

**Table 2 T2:** Schedule of measurements and trial activities

	Visits				
	Telephone screening	Enrolment visit	Baseline visit	4-week follow-up	8-week follow-up
Enrolment					
Eligibility screening	X				
Informed consent		X			
Randomisation			X		
Intervention					
Replacing meat with alternative plant-based product					
Control					
Demographic and psychosocial traits					
Demographics			X		
Food neophobia			X		
Self-control scale			X		
Dietary measurements					
Food diary			X	X	X
Retrospective eating questionnaire			X	X	X
Psychosocial variables					
Attitude towards eating a low meat diet and using meat alternatives			X	X	X
Perceived behavioural control of eating a low meat diet and using meat alternatives			X	X	X
Subjective social norm of eating a low meat diet and using meat alternatives			X	X	X
Intention to eat a low meat diet and to use meat alternatives			X	X	X
Attachment to meat			X	X	X
Eating identity			X	X	X
Desire for similarity between meat and meat alternatives			X	X	X
Biophysical outcomes					
Height			X		
Weight			X	X	X
Body composition			X	X	X
Blood pressure			X	X	X
Blood lipids profile			X	X	X
Qualitative workstream					
Semistructured interviews					X

### Sociodemographic characteristics

At the baseline, participants will be asked to self-report on their age, sex, highest degree, household income, household composition, ethnicity and nationality.

### Psychological trait characteristics

At the baseline, participants’ trait food neophobia will be measured using a questionnaire scale adapted from Pliner and Hobden^35^ including six items with a 7-point scale (disagree strongly—agree strongly).At the baseline, participants’ self-control will also be assessed using a questionnaire scale adapted from Tangney^36^ including eight items with a 7-point scale (disagree strongly—agree strongly).

### Dietary measurements

Meat consumption will be measured in grams/day by disaggregating meat products recorded by participants on their 7 days food diaries. The daily average will exclude days in which energy intake was <1000 kcal, which are considered unlikely to represent habitual consumption.Average daily number of meals containing foods from other food groups will be measured counting the meals in participants’ food diaries containing the food groups of interest, including:Unprocessed pork meat.Unprocessed red meat from ruminants.Unprocessed poultry or game meat.Processed meat.Mycoprotein meat alternatives.Soy-based meat alternatives or meat alternatives made of other textured vegetable protein.Other meat alternatives (eg, bean burgers).Milk and yoghurt.Cheese.Dairy-free milk and yoghurt alternatives.Dairy-free cheese alternatives.Fish and seafood.Eggs.Pulses other than those in meat alternatives.Vegetables other than those in meat alternatives.Starchy foods other than those in meat alternatives.Nuts and seeds other than those in meat alternatives.Fruit.Savoury and sweet snacks.Soft drinks.Alcoholic drinks.A retrospective eating questionnaire will also ask participants to recall the number of eating occasions on which they had the foods listed above over the week of their food diary. This questionnaire will only be used in sensitivity analyses.The daily average energy intake and nutritional composition of participants’ diets will be measured using data from the online food diary.

### Psychosocial variables

Attachment to meat will be measured using the meat attachment questionnaire.^37^Eating identities will be self-reported by participants among meat eater, omnivore, flexitarian, pescatarian, vegetarian, vegan or ‘other’.Attitudes, subjective social norms and perceived behavioural control to eat a low meat diet and to use meat alternatives will be, respectively, assessed with three questionnaire items constructed following Francis *et al*
38 on a 7-point scale (disagree strongly—agree strongly).Intentions to eat a low meat diet and to use meat alternatives will be assessed using a single questionnaire item on a 7-point scale (disagree strongly—agree strongly).Desire for similarity between meat and meat alternatives will be assessed using 11 questionnaire items with a 7-point scale (disagree strongly—agree strongly) adapted from Hoek *et al*.^25^

### Physical measures

Blood lipids profiles (total cholesterol, HDL cholesterol, triglycerides, LDL cholesterol, non-HDL cholesterol, LDL:HDL cholesterol ratio) will be measured using Alere Cholestech LDX.Height will be measured to the nearest 0.1 cm using a stadiometer.Weight and body composition will be measured using an electronic scale (SC-240 MA, Tanita, Japan), which records the proportion of body fat using bioelectrical impedance. Weight was recorded to the nearest 0.1 kg.Seated blood pressure will be measured as the average of the second and third reading of three seated readings

### Retention

We will use reminder text messages to increase attendance to each of the four study appointments. Additionally, participants will receive financial compensation for partaking in each of the three assessment visits. Participants will have the right to withdraw from the study at any time. The principal investigator will have the right to discontinue participants’ involvement in the study when they become ineligible and/or when significant protocol deviations occur. The data of participants who withdraw will be kept and might be used in exploratory and sensitivity analyses, unless the participant requests for the data to be deleted.

### Adverse events

Any study-related adverse event will be reported to the research ethics committee in accordance to Good Clinical Practice (GCP). All study-related adverse events will be included in the final trial report.

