#### Follow-up

Participants will be invited to attend a 4-week (T1) and an 8-week (T2) follow-up and to keep a 7-day food diary over the week leading up to each follow-up. During the follow-up appointments, a member of the research team will collect the respective food diary, ask participants to answer an online questionnaire and measure participants blood lipids profile, blood pressure, weight and body composition.

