### Randomisation and blinding

Participants’ group allocation will be based on a computer-generated randomisation sequence, produced by an independent statistician. The randomisation sequence was designed to individually allocate participants to the intervention or control condition in a 1:1 ratio and to achieve a proportional gender balance in the two conditions through blocking and stratification by sex. The research team is blinded to the randomisation sequence and to its block sizes and sequence. Allocation will be revealed to the researcher performing the randomisation only after the first food diary has been returned. Due to the nature of the intervention, participants and some members of the research team cannot be blind to participants’ group allocation. The members of the research team analysing the food diaries will be blind to the group allocation. Due to the nature of the outcomes, the risk of investigator bias will be low. To address the risk of social desirability bias in participants’ reporting of foods intake and questionnaire responses, participants will be reminded during the enrolment visit and before each questionnaire that there are no right or wrong answers.

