### Comparator

Participants in the control condition will receive no intervention. The template for intervention description and replication (TiDIER) checklist^34^ for the Re-MAP intervention and the comparator is reported in table 1.

**Table 1 T1:** TiDIER checklist describing the replacing meat with alternative plant-based product (Re-MAP) intervention and no-intervention comparator

	Intervention	Comparator
Brief name	Re-MAP—a behavioural intervention to reduce meat consumption	No intervention
Why	Environmental restructuring: Meat alternatives will be provided for 1 month with the aim of enhancing attitudes towards and behavioural control of eating a low meat diet by making meat-free alternative easily available to participants. This intervention component also aims to reduce participants’ attachment to meat. Participants will select from a range of commercially available meat alternatives including soy and other textured vegetable protein products (eg, soy sausages), plant-based and pulse-based products (eg, bean burgers), mycoprotein products (eg, mycoprotein steaks). Meat alternatives will be defined as meat-free products that fulfil the same gastronomic function as products that normally contain meat (eg, sausages, burgers, meatballs, steaks or mince). Training: Recipes will be provided with the aim of enhancing participants’ behavioural control of eating a low meat diet by enhancing their skills of preparing meat-free meals. Education: Information leaflets about the health and environmental benefits of eating less meat will be provided to enhance participants’ attitudes towards eating a low meat diet and to reduce participants’ attachment to meat. Social modelling: Written success stories of people who reduced their meat consumption will be provided to increase participants perceived social norm of eating a low meat diet and to promote the dietary identity of meat reducers, such as flexitarians.	N/A

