### Statistical analyses

We will employ linear models to investigate whether changes in meat consumption between the baseline and both follow-up differ significantly between the intervention and the control group. Our main analysis will employ unadjusted models and only include data from participants completing the relevant follow-up. Sensitivity analysis will be performed with a baseline observation carried forward assumption for missing data and adjusting for baseline variables. The intervention effect will be reported with 95% CI and p values. A two-tailed criterion p value of alpha=0.05 will be used to assess the statistical significance of the results. The same procedure will be employed to assess whether changes in the other prespecified dietary, nutritional, psychosocial and biophysical outcomes between the baseline and both follow-up differ significantly between the control and the intervention group. Detailed main, subgroup and sensitivity analyses plans will be finalised before conducting any specific outcome analysis. No interim analysis is planned.

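### The adverse-event commitment covers only study-related events, so in this open trial with an untreated control arm the reported counts may not be comparable between arms

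*Protocol article*

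**What the plan says.** The Adverse events section of the protocol article has two sentences. The first sends study-related adverse events to the research ethics committee under GCP. The second fixes the content of the publication: "All study-related adverse events will be included in the final trial report". No commitment is made for other events.

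Three other parts of the article bear on how that rule will work:

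- **Comparator:** "Participants in the control condition will receive no intervention". Table 1 describes what the other arm gets: soy and other textured vegetable protein, pulse-based and mycoprotein products, supplied for the intervention month.
- **Randomisation and blinding:** "participants and some members of the research team cannot be blind to participants’ group allocation". The one task stated to be done blind to allocation is diary analysis: "The members of the research team analysing the food diaries will be blind to the group allocation".
- **Follow-up:** at both follow-up visits a team member will "ask participants to answer an online questionnaire and measure participants blood lipids profile, blood pressure, weight and body composition". This section makes no distinction between arms.

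**The concern.** Randomisation supports a fair comparison of all events collected alike in both arms. It does not protect a subset chosen by a causal judgement when those reporting or judging the events may know the allocation. Take a minor complaint such as a digestive upset (my example; the article names none). In the intervention arm there are new foods to blame. In the control arm there is little beyond the visits and measurements, which both arms share. The same complaint may therefore pass the filter more readily in one arm than in the other.

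Two errors are possible. Unequal attribution could make the products look as if they cause complaints when the true rates are equal. Sparing attribution could remove most of a real excess from view. The stake is modest but real, because the article's list of strengths presents the trial as giving preliminary evidence on the health implications of replacing meat with alternatives. Readers will look at the adverse events in that light.

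**Working it through.** **The plan's own figures.** The article gives no adverse-event rate, no attribution probability and no planned test of adverse events, so there is no figure to reproduce. The point rests on reading the sections together. The arithmetic below only shows how the filter behaves.

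**Step 1: what the rule selects.** An event falls under the reporting commitment if it occurs and is judged study-related. With n participants in an arm, true event risk r (at most one event per person) and probability a that an event is judged related, the expected number reported is

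E = n × r × a.

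If n and r are the same in both arms, the ratio of expected reported counts is a(intervention) / a(control). The true risk cancels. Reported counts are comparable only if attribution is the same in both arms.

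**Step 2: inputs.** n = 50 per arm, from the target of at least 100 completers (Sample size) and 1:1 allocation (Randomisation and blinding). The remaining inputs are assumptions: r from 10% to 30%, equal in both arms; a = 50% in the intervention arm; a from 50% down to 10% in the control arm.

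**Step 3: results with no true difference.** For the intervention arm at r = 20%, E = 50 × 0.20 × 0.50 = 5.0. The other cells follow the same formula.

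| True risk, both arms | Intervention, a = 50% | Control, a = 50% | Control, a = 25% | Control, a = 10% |
|---|---|---|---|---|
| 10% | 2.5 | 2.5 | 1.25 | 0.5 |
| 20% | 5.0 | 5.0 | 2.5 | 1.0 |
| 30% | 7.5 | 7.5 | 3.75 | 1.5 |

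The ratios across the three control columns are 0.50/0.50 = 1, 0.50/0.25 = 2 and 0.50/0.10 = 5, whatever the true risk. The control count is zero only in the limit where no control event can be judged related, and the article states no such limit.

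**Step 4: the opposite error.** Suppose the true risks are 20% and 10%. Without the filter the expected counts are 50 × 0.20 = 10 and 50 × 0.10 = 5. If only 10% of events are judged related in each arm, they become 10 × 0.10 = 1.0 and 5 × 0.10 = 0.5. The ratio survives, but almost nothing is left to see.

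**Step 5: do other planned measures fill the gap?** The Statistical analyses section applies the same models to the remaining outcomes, testing if "changes in the other prespecified dietary, nutritional, psychosocial and biophysical outcomes between the baseline and both follow-up differ significantly between the control and the intervention" arms. Lipids, blood pressure, body mass index and body fat are thus compared with no attribution filter. They do not record symptoms or reactions to the foods.

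**The case against.** The strongest reply is that the rule is a minimum. It says study-related events will be included; it does not say that others go unrecorded or unpublished. Adverse events are not among the primary, secondary or exploratory outcomes, and no between-arm test of them is planned. How events are defined, collected and judged is commonly left to a full protocol, which is not shown. The products are on general sale, people with relevant food allergies are excluded, and the intervention lasts 4 weeks.

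Much of this stands. The absence of definitions, collection methods or a named assessor is no finding, and I rely on none of it. No p-value belongs here, since no test is planned. The consequence is limited.

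What the reply does not remove is the rule that the article does state. Relatedness marks the boundary of the reporting commitment, and that is a poor boundary in an open trial with an untreated control arm. Even without a formal test, readers will compare the counts in a two-arm report.

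A reader might go further and infer that the report is one-sided by construction, or that background events are removed from one arm only. The article does not support this. The wording is study-related, not intervention-related. Controls attend the same visits and have the same measurements, including blood lipids, so an event they suffer from those procedures would qualify. An event judged unrelated falls outside the commitment in either arm. Nor does the article say who assesses relatedness, so it cannot be asserted that this person knows the allocation. What is stated is that participants and some staff do, and that no blinding is described beyond the diary analysis.

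**Conclusion.** The point holds as a risk that depends on attribution; an imbalance is not certain. If attribution differs between arms, reported counts will differ with equal true rates, in the ratio of the attribution probabilities. The article gives neither event rates nor attribution probabilities, so the direction and size cannot be computed. On the assumed values the ratio runs from 1 (equal attribution) to 5 (50% against 10%). Severity is low: the primary outcome and its analysis do not depend on this rule. It is worth correcting because a less biased rule costs little.

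**What to change.** In the Adverse events section, collect adverse events in the same way in both arms, for example with one identical open question on new health complaints at the existing 4-week and 8-week visits. State that all recorded events will be reported by arm regardless of attribution, with the relatedness judgement shown as a descriptive column and not used as a filter. Reporting to the ethics committee stays as written.

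The cost is one question at two visits that already take place, slightly more data entry and one extra table. The sample size and the primary analysis do not change.

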### Data management

Data will be entered by a trained member of the research team and stored in an OpenClinica database that was specifically developed for this trial. The database will feature ranges and validation checks to promote reliability in the data entry process. Data recording and storage will run in accordance with GCP.

### Statistical analyses

We will employ linear models to investigate whether changes in meat consumption between the baseline and both follow-up differ significantly between the intervention and the control group. Our main analysis will employ unadjusted models and only include data from participants completing the relevant follow-up. Sensitivity analysis will be performed with a baseline observation carried forward assumption for missing data and adjusting for baseline variables. The intervention effect will be reported with 95% CI and p values. A two-tailed criterion p value of alpha=0.05 will be used to assess the statistical significance of the results. The same procedure will be employed to assess whether changes in the other prespecified dietary, nutritional, psychosocial and biophysical outcomes between the baseline and both follow-up differ significantly between the control and the intervention group. Detailed main, subgroup and sensitivity analyses plans will be finalised before conducting any specific outcome analysis. No interim analysis is planned.

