#### Baseline

Following the enrolment appointment, participants will complete a 7-day food diary over the week leading up to the following appointment, the baseline (T0). Participants not keeping sufficiently detailed diaries and those eating meat on less than five eating occasions over the week will be discontinued. At the baseline appointment, an appropriately trained member of the research team will collect participants’ food diaries, ask participants to answer the baseline online questionnaire and measure participants blood lipids profile, blood pressure, weight and body composition. At the end of the baseline appointment, participants will be randomised to one of the two study conditions and will then follow the respective protocol for the next 4 weeks.

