### Sample size

Due to lack of research studies directly comparable to ours, pragmatic considerations have guided the decision to terminate recruitment once a sample of at least 100 volunteers has completed the 4 weeks follow-up. A power analysis based on this pragmatically selected sample size suggests that 100 participants completing the primary outcome will allow detection of a medium effect size of d=0.6 with a power of 1-beta=0.84 and a two-tailed alpha criterion of 0.05.

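### The main analysis compares unadjusted changes in meat intake; a model adjusted for baseline intake would be at least as precise and would guard against chance imbalance

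*Protocol article*

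**What the plan says.** All references are to the protocol article.

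- **Primary outcome** is the T0-to-T1 change in average daily meat intake in grams, from 7-day food diaries.
- **Statistical analyses** fixes the model: "Our main analysis will employ unadjusted models and only include data from participants completing the relevant follow-up". Adjustment appears one sentence later: "Sensitivity analysis will be performed with a baseline observation carried forward assumption for missing data and adjusting for baseline variables". The baseline variables are not named. The same procedure is then extended to the other dietary, nutritional, psychosocial and biophysical outcomes.
- **Sample size**: recruitment stops on pragmatic grounds, the rule being to "terminate recruitment once a sample of at least 100 volunteers has completed the 4 weeks follow-up". The power statement is "detection of a medium effect size of d=0.6 with a power of 1-beta=0.84 and a two-tailed alpha criterion of 0.05".
- **Baseline**: participants who do not keep sufficiently detailed diaries are discontinued, and "those eating meat on less than five eating occasions over the week will be discontinued". Randomisation takes place at the end of that appointment.
- **Randomisation and blinding**: allocation is 1:1, blocked and stratified by sex only, and is revealed after the first diary is returned.

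**The concern.** A comparison of changes subtracts each participant's baseline in full, so the baseline coefficient is fixed at 1. A single diary week is a noisy measure of habitual intake. When the slope of follow-up on baseline is below 1, full subtraction over-corrects, and part of the baseline noise is carried into the estimate.

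Two things are at stake. The first is precision, in a trial whose size was set pragmatically and whose power is 0.84. The second is sensitivity to chance: nothing in the design balances baseline meat intake, and if the arms happen to differ on it, the unadjusted estimate moves in a predictable direction. Both carry over to every continuous outcome analysed in the same way.

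**Working it through.** **Inputs from the protocol.** 100 completers, taken as 50 per arm (1:1); d = 0.6; two-sided alpha 0.05; stated power 0.84.

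**Assumptions, not in the protocol.** The correlation r between baseline and follow-up intake, shown over 0.3 to 0.9; equal SD σ at T0 and T1 (relaxed in step 4); d = 0.6 expressed on the SD of change (relaxed in step 5).

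**1. The stated power.** A two-sample t-test with 50 per arm, d = 0.6 and 98 df gives 0.844; the normal approximation gives 0.851. The stated 0.84 reproduces.

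**2. Precision.** Per-participant variance is 2σ²(1−r) for change and σ²(1−r²) after adjustment for baseline. The ratio adjusted/unadjusted is (1−r²)/[2(1−r)] = (1+r)/2. CI width scales with its square root. Equivalent completers are 100 divided by the ratio. Power uses the noncentral t with 97 df and d = 0.6/√((1+r)/2).

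| r | Variance ratio | 95% CI narrower by | Power, adjusted (unadjusted 0.844) | Equivalent completers |
|---|---|---|---|---|
| 0.3 | 0.65 | 19% | 0.958 | 154 |
| 0.5 | 0.75 | 13% | 0.929 | 133 |
| 0.7 | 0.85 | 8% | 0.896 | 118 |
| 0.9 | 0.95 | 2.5% | 0.862 | 105 |

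**3. Chance imbalance.** If the baseline means differ by D, the unadjusted estimate shifts by −(1−r)D. One standard error of D is σ√(2/50) = 0.2σ. The target effect is 0.6σ√(2(1−r)), and the standard error of the change comparison is 0.2σ√(2(1−r)).

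| r | Shift for a one-SE imbalance | As share of target effect | In SEs of the estimate | Conditional type I error, two-SE imbalance |
|---|---|---|---|---|
| 0.3 | 0.14σ | 20% | 0.59 | 0.168 |
| 0.5 | 0.10σ | 17% | 0.50 | 0.134 |
| 0.7 | 0.06σ | 13% | 0.39 | 0.101 |
| 0.9 | 0.02σ | 7% | 0.22 | 0.067 |

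Worked line at r = 0.5 with a two-SE imbalance: rejection limit 1.96 × 0.2σ = 0.392σ; shift 0.2σ; conditional SD 0.2σ√0.75 = 0.173σ. The upper-tail probability beyond (0.392−0.2)/0.173 = 1.11 is about 0.134, and the other tail is negligible. After a one-SE imbalance the conditional type I error stays between 0.046 and 0.050.

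**4. Unequal SDs.** With k = SD(T1)/SD(T0), the variance ratio is k²(1−r²)/(k²+1−2rk). It equals 1, so nothing is gained, when rk = 1 (for example r = 0.8 with k = 1.25, or r = 0.5 with k = 2). At r = 0.7 and k = 1.2 it is 0.7344/0.76 = 0.97.

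**5. If d = 0.6 is on the raw SD.** Power for change against adjusted is 0.709 against 0.876 (r = 0.3), 0.844 against 0.929 (r = 0.5) and 0.970 against 0.986 (r = 0.7).

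**6. Selection on the baseline diary.** A null simulation (20,000 runs, 50 per arm) kept only participants with baseline above −0.5 SD, with r = 0.5 before truncation. The unadjusted comparison had mean estimate −0.002 and type I error 0.051; the adjusted model had −0.001 and 0.049. The SDs of the estimates were 0.188 and 0.175. That is 7% narrower (0.175/0.188 = 0.93), not 13%, because truncation shrinks the baseline SD and so raises k.

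**The case against.** The strongest defence is that the planned test is legitimate. It is pre-specified, matches the stated outcome, controls type I error, is unbiased over randomisation and delivers its own power figure. An adjusted analysis is already planned, and the detailed plans are still to be finalised before outcome analysis. On this view the point is only which of two valid analyses is called primary, with a gain that depends on an unstated r. All of those facts stand. They do not remove the point. The choice of an unadjusted main model is stated, not left open, and the headline estimate, CI and p value will come from it. The list of covariates may properly sit in a statistical analysis plan, and its absence here is not the complaint.

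A reader might infer four stronger things that the document does not support:

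- **That the change score throws the baseline away.** It uses it, with a coefficient of 1 instead of an estimated slope.
- **That the five-occasion threshold biases the result through regression to the mean.** The diary and the threshold precede randomisation, so both arms are selected alike and regress alike in expectation. Step 6 shows no bias and no inflation of type I error. Regression to the mean matters here only through chance imbalance.
- **That change is less precise whenever r is below 1.** This needs equal SDs; precision is equal when rk = 1. Selection on the baseline week tends to push k above 1 and so to reduce the gain.
- **That the power statement is wrong.** It reproduces.

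**Conclusion.** The point holds as one of efficiency and robustness, not validity. Asymptotically, the unadjusted comparison is never more precise than the model adjusted for baseline intake, and it is usually less precise. Under equal SDs and d = 0.6 on the SD of change, the gain runs from substantial at r = 0.3 to slight at r = 0.9. It is smaller where the follow-up SD exceeds the baseline SD, and vanishes at rk = 1. The protocol gives neither r nor the SDs, so the size cannot be fixed more closely. Overall type I error is sound. What the unadjusted analysis lacks is protection in the particular sample drawn: a one-SE baseline imbalance moves its estimate by 7% to 20% of the target effect over the same range of r. This should be changed because the remedy is almost free, not because the planned analysis would be wrong.

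**What to change.** In Statistical analyses, make the main model at T1 and at T2 a linear regression of mean daily grams of meat on arm, with baseline mean daily grams as a covariate and, ideally, the stratification factor sex. Using the change as the dependent variable with the same covariates gives the identical arm effect, so the primary outcome definition need not alter. Move the unadjusted comparison of changes to the sensitivity analyses. Analyse each continuous secondary and exploratory outcome in the same way, adjusted for its own baseline value.

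The cost is a sentence or two, recorded before any outcome analysis. No new data are needed, since every participant returns a baseline diary before allocation is revealed. The sample size statement can stay; under its own d, read on the SD of change, and equal SDs, 0.84 becomes a conservative figure over the range of r shown.
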